**Figure 1 F1:**
[figure not shown]
Flow diagram of the progress from screening to the final follow-up assessment.

### Intervention

#### Osteo-cise: Strong bones for life program

*Osteo-cise: Strong Bones for Life* is a community-based program that includes four key components: 1) Osteo*-cise*: a multi-modal targeted osteoporosis and falls prevention exercise program; 2) Osteo*-Adopt*: a behavioural change program designed to optimise adherence to the Osteo-*cise* program; 3) Osteo*-Ed*: an osteoporosis awareness and education program for the study participants, and 4) Osteo*-Instruct*: a train-the-trainers workshop designed to update the exercise trainers with the latest osteoporosis prevention and management information and to instruct them on the aims and structure of the program. The structured exercise program is designed to run over 12 months and to be conducted within local community leisure or recreational health facilities under the supervision of *Osteo-cise* trained exercise instructors. Managers of local health and fitness centres within the western suburbs of Melbourne will be contacted by phone and invited to participate in the study. All interested managers and relevant staff will be given a detailed presentation outlining the program and requirements. Those that agree will then be asked to recommend suitably qualified exercise trainers to undertake the Osteo-*Instruct* ‘train-the-trainers’ workshop to implement the exercise program at their facility. Specific details on the program’s four key components are provided below.

##### *1. ‘*Osteo*-cise’: Targeted Osteoporosis Exercise Program*

Participants randomised to the Osteo*-cise* group will be instructed to train at their nearest *Osteo-cise* health and fitness centre on three non-consecutive days per week for 18 months. The gymnasium membership for all participants during the initial 12 months will be subsidised. Exercise sessions will be conducted in small groups (a maximum of 10 per group) and monitored by qualified and certified exercise trainers who have completed the Osteo-*Instruct* training workshop. Before commencing the program, all participants will be required to attend an orientation session at their selected leisure facility to become familiar with the aims and design of the training program and the rules and regulations of each health and fitness centre.

The initial 12 months of the *Osteo-cise* program will be divided into a 4-week ‘Adoption Phase’ followed by four distinct 12-weekly mesocycles (Table 2). Each mesocycle is further divided into three 4-weekly microcyles which are designed to promote a sense of achievement and become progressively more challenging. Every session of the 4-week ‘Adoption Phase’ and the first week of each mesocycle will be supervised by *Osteo-cise* trainers. For the remaining 11 weeks of each mesocycle, participants will attend one scheduled supervised session per week with their designated trainer and two additional sessions independently or with fellow participants. All participants will be instructed to consult other on-site gym staff if they require assistance with their exercise program. Each session is intended to take approximately 60 minutes to complete and will comprise of a warm-up, high velocity progressive resistance training (HV-PRT) using machine and free weights, moderate impact weight-bearing exercises, high challenge balance and mobility exercises, core muscle stabilization exercises and flexibility (stretching) exercises. All programs will be individually tailored and designed to follow the key training principles of specificity and progressive overload. To assist trainers with exercise selection for each participant and to ensure correct technique and exercise progression, trainers will be provided with an *Osteo-cise* exercise manual which will include detailed explanations and illustrations for all key exercises.

**Table 2 T2:** **Structure of the ****
*Osteo-cise: Strong Bones for Life *
****exercise program and training doses for 12-months**

**Mesocycle**		**Microcycle**	**Intensity**	**High-Velocity PRT**				**Impact Exercises**			**Functional Training**		
**Phase**	**Week**	**Training Phase**	**RPE**^ **1** ^	**Sets**	**Reps**	**Speed**^ **2** ^	**Rest**	**Sets**	**Reps**	**Rating**^ **3** ^	**Sets**	**Reps**	**Progression**
#1	1-2	Orientation to	3 - 4	2	12-15	Slow	1-2	3	10-20	Low	2		Fit Ball and
	3-4	Training	3 - 4	2	12-15	Slow	1-2	3	10-20		2		Standing Balance
#2	5-8	Preparatory #1	3 - 4	2	10-15	Slow	1-2	3	10-20	Low	2		Fit Ball and
	9-12	Challenge #1	5 – 8	2	8-12	Rapid	2	3	10-20	to	2		Standing Balance
	13-16	Consolidation #1	5 – 8	2	8-12	Rapid	2	3	10-20	Moderate	2	All	
#3	17-20	Preparatory #2	3 - 4	2	10-15	Slow	1-2	3	10-20	Moderate	2	functional	Standing Balance
	21-24	Challenge #2	5 – 8	2	8-12	Rapid	2	3	10-20		2	training	and Dynamic
	25-28	Consolidation #2	5 – 8	2	8-12	Rapid	2	3	10-20		2	30-60	Functional
#4	29-32	Preparatory #3	3 - 4	2	10-15	Slow	1-2	3	10-20	Moderate	2	seconds or	Standing Balance
	33-36	Challenge #3	5 – 8	2	8-12	Rapid	2	3	10-20	to	2	until fatigue	and Dynamic
	37-40	Consolidation #3	5 – 8	2	8-12	Rapid	2	3	10-20	High	2		Functional
#5	41-44	Preparatory #4	3 - 4	2	10-15	Slow	1-2	3	10-20	High	2		Standing Balance
	45-48	Challenge #4	5 – 8	2	8-12	Rapid	2	3	10-20		2		and Dynamic
	49-52	Consolidation #4	5 – 8	2	8-12	Rapid	2	3	10-20		2		Functional

^1^ RPE = Rating of Perceived Exertion; ^2^ Speed: slow speed = traditional resistance training (2–3 sec concentric and 2–3 sec eccentric contractions); rapid speed = high velocity training (rapid concentric and 2–3 sec eccentric contractions); ^3^Impact rating: Low = Ground Reaction Force (GRF) ~ 1–3 x body weight, Moderate = GRF ~ 3–6 x body weight, High = GRF ~ 6–9 x body weight: Rest in minute.

a) High velocity progressive resistance training (HV-PRT) or power training

HV-PRT is a type of resistance training whereby the concentric (lifting) phase of the exercise is performed as rapidly as possible in order to maximise both movement speed and muscle force. A combination of pin-loaded machine weights, pulleys and free weights will be used to overload the specific muscle groups that attach to skeletal sites prone to osteoporotic fracture, particularly the hip and spine. Trainers will be advised to choose from the following core exercises: squats, leg press, lunges, bench step ups, hip extension, hip flexion, hip abduction, hip adduction, calf raises, back extension, lateral side bends, latissimus dorsi pull down (or seated row) and a combination of abdominal and core stability exercises. Where possible, participants will be asked to perform the exercises whilst standing in an attempt to optimise balance and muscle function. Additional exercises including bench press, military press, bicep curls, tricep extension and shoulder, lumbo-pelvic and spine stabilisation exercises will also be rotated throughout the program to ensure the development of muscle balance. For each exercise card a total of six resistance exercises will be performed in each training session, with new exercises introduced into the program at the beginning of each new mesocycle (i.e. every 12 weeks) where appropriate.

Table 2 outlines the recommended training intensity and the number of sets and repetitions to be completed during each training phase of the 12-month structured program. Training during the first 4 weeks (Adoption phase) will be at low intensity and low velocity to allow the participants to master the correct lifting techniques and to become familiar with the training principles. Thereafter, the emphasis of the program will shift to HV-PRT for the lower extremity exercises. Exercise intensity will be monitored by the trainers using the Rating of Perceived Exertion scale (RPE), or the Rating of Perceived Difficulty for balance exercises, on the modified BORG 1 to 10 RPE scale. Participants will be expected to exercise at a level that corresponds to an RPE of between 5 and 8, which represents hard to very hard exertion.

b) Moderate impact weight-bearing exercise

The weight-bearing impact exercise component of the program will consist of a series of lower limb exercises aimed at specifically loading the hip. We have developed a battery of 27 bone friendly exercises which were found to be safe and effective for improving femoral neck and lumbar spine BMD in middle aged and elderly men [36,37]. Trainers will select appropriate weight-bearing exercises from the *Osteo-cise* manual based on each participant’s ability and/or on the existence of any previous medical conditions (e.g. knee osteoarthritis). Exercises are divided into three categories: Level 1 - Stationary movements (e.g. stomping, mini tuck jumps); Level 2 - Forward/Backward movements (e.g. box step-ups, backward and forward pogo jumps); and Level 3 - Lateral/Multidirectional movements (e.g. side-to-side shuffle, lateral box jumps). Each category has three levels (Easy, Moderate, Hard) based on the degree of difficulty and the magnitude of the impact forces (ground reaction forces) associated with each exercise [36]. A total of two to three weight-bearing impact exercises will be included in each training session. For each exercise, participants will perform three sets of 10 to 20 repetitions per session, equating to a total of 60 to 180 impacts per session. This dose was shown to be effective for increasing hip and spine BMD in our previous intervention in older men [36]. Training intensity will be progressively increased by increasing the height of jumps and/or by adding additional weight (i.e. holding dumbbells, weighted vest) or introducing multidirectional movement patterns.

c) Balance and mobility training

The balance training component will incorporate a variety of static and dynamic balance exercises aimed at improving posture and anticipatory/reactive balance and mobility. Exercises will fall into three categories: 1) Fit-ball exercises (e.g. fit-ball sitting with heel lifts), 2) Standing balance exercises (e.g. single leg standing), and 3) Dynamic functional exercises (e.g. heel-toe walking). Two challenging balance exercises will be performed in each session, with each exercise held for up to 30 seconds (e.g. 30 seconds of single leg standing) or performed for a given number of repetitions (e.g. 10 to 20 lateral weight shifts whilst sitting on a fit-ball). Once an exercise is no longer challenging for the participant they will be instructed to progress to the next level of difficulty by changing the exercise using the following progressions: closing eyes, reducing base of support, confounding visual fixation (e.g. head turns), changing centre of mass (e.g. arm/leg lifts) or adding a secondary manual or cognitive task. The type of balance exercises and starting level of difficulty will be prescribed by the trainer according to each participant’s functional ability.

d) Core and hip muscle stabilisation exercises

The key muscle groups targeted in this component of the exercise program include the rotator cuff (supraspinatus, infraspinatus, teres minor and subscapularis), scapular stabilisers (middle and lower trapezius, rhomboid major and minor, and serratus anterior), transverse abdominis and pelvic floor muscles. These muscles help to maintain good posture and trunk stability, which are important for balance and maximising muscle power [38]. Participants will complete two stabilising exercises per session using light to moderate resistance. For the rotator cuff and scapular stabilizers exercises, participants will perform two sets of 10 to 15 repetitions and up to 50 repetitions for the abdominals.

##### *2. ‘Osteo-Adopt’: Implementation of behavioural modification strategies*

An important component of this study is to develop a holistic community-based program that will provide older adults with the skills required to manage their own musculoskeletal health and promote behaviours that encourage adoption and maintenance of lifelong exercise participation. Increasing each participant’s motivation and readiness to exercise is crucial for long-term maintenance of musculoskeletal health. Consequently, widely established behavioural principles, particularly the Transtheoretical (Stages of Change) Model (TTM) and Social Cognitive Theory, will be utilised to initiate exercise adoption and guide long-term maintenance [30,31]. Fundamental to the TTM model are a number of cognitive and behavioural strategies that help individuals progress from lower to higher levels of motivational readiness, with the aim of modifying attitudes and fostering specific behaviours. Several approaches for improving adoption and adherence to exercise programs will be applied, including social support for physical activity, positive and social reinforcement, overcoming bar1riers to behaviour change, goal setting and self-monitoring.

Social support will be enhanced by organising participants into small exercise groups that facilitate socialisation and interaction. The development of relationships with other participants in the *Osteo-cise* program (‘buddy’ system) and telephone calls from the research staff or exercise trainers will also be used to optimise enjoyment of the program and hence adherence, as will quarterly newsletters aimed at providing information of interest (e.g. study updates, upcoming events and relevant scientific findings). In addition, at 3-monthly intervals trainers will ask participants to complete a Behavioural Evaluation Form which requires the establishment of short- and long-term exercise goals and helps to recognise motivating factors and potential barriers to attaining these goals. Strategies to overcome these barriers may then be identified and discussed by participants together with their trainer. Trainers will also endeavour to prevent lapses by calling participants who have missed three consecutive training sessions and discuss strategies to improve adherence. Finally, positive reinforcement will be achieved through self-monitoring of progression marked by the completion of the exercise cards.

##### *3. ‘Osteo-Ed’: Osteoporosis education and awareness program*

Participants will be invited to attend three osteoporosis-related community educational seminars presented by the research staff. These sessions will aim to improve knowledge and understanding of risk factors and preventative measures for osteoporosis, falls and fractures so that participants are encouraged to actively manage their health. The content of Osteo*-Ed* will be adapted from educational resources developed by Osteoporosis Australia that are based on current scientific evidence. Topics covered will include: 1) Osteoporosis – What are the risk factors?; 2) Exercise for optimal bone and muscle health; and 3) Nutrition for healthy bones. The Osteo*-Ed* seminars are intended to be informal sessions whereby questions and open discussion are encouraged. Each will run for approximately 60 minutes and will take place at selected *Osteo-cise* community leisure centres.

##### *4. ‘Osteo-Instruct’: Exercise instructors training workshop*

All exercise trainers employed to work on the *Osteo-cise: Strong Bones for Life* program will be required to attend a one-day training workshop that will cover information about the latest research on osteoporosis and falls; current treatment and management options; challenges facing older adults with or at risk of osteoporosis; basic nutrition for healthy bones; the benefits of exercise for preventing and managing osteoporosis and falls, including the most appropriate type, mode, intensity and frequency of training; safe exercise progressions; contraindicated exercises; and behavioural management strategies to enhance compliance to exercise. In addition, the Osteo*-Instruct* workshop will teach trainers how to identify early cues to poor adherence and strategies to prevent lapses and promote individuals’ self-confidence in their ability to undertake the exercise program. Importantly, the workshop will also familiarise the trainers with the design and specific aims of the *Osteo-cise* program. All trainers will be provided with a copy of the *Osteo-cise* training manual, which will contain all the essential information that is needed to implement the training program. This includes the rationale behind the program, training principles for optimal bone health, and a detailed description of each program component including progressions of exercise volume and intensity as well as illustrations of recommended exercises. Safety considerations, such as injury prevention and exercises to avoid for various disease states, will also be clearly highlighted in the trainer’s manual.

Trainers will be provided with a folder containing each study participant’s personal details, including relevant medical history and a copy of their physician's approval to exercise. Trainers will be required to document any contact made with participants throughout the intervention in this folder as well as any injuries or adverse events that occur as a result of the exercise sessions. The research team will maintain regular contact with the trainers and visit all health and fitness centres during each training cycle to ensure that the trainers are up-to-date with the program and that the quality of the program is being upheld and delivered as intended.

### Self-management control group

The self-management control group will serve as the comparison group in the intervention. Participants assigned to this group will receive general consumer information taken from Osteoporosis Australia fact sheets, including: “What is osteoporosis?”, “What are the risk factors for osteoporosis?” and “Calcium, vitamin D and exercise tips for preventing osteoporosis”. The aim is to enable these participants to actively take charge of their own musculoskeletal health and make educated decisions to seek further medical information and appropriate services to help prevent osteoporosis, falls and fractures. This group will undertake exactly the same testing protocol as the intervention group, but will not participate in the structured *Osteo-cise* program.

### Calcium and vitamin D supplementation

To ensure that daily calcium intakes meet the current recommended dietary intake of 1000 to 1300 mg/d for men and women aged over 50 years and that vitamin D levels are close to optimal (at least 60 to 75 nmol/L), participants in both groups will be requested to consume 2x350 mg elemental calcium tablets (Blackmores Total Calcium) and a single 1000 IU vitamin D_3_ capsule (Blackmores Vitamin D_3_) each day. All supplements will be provided free of charge.

### Follow-up period

During the final 6-month *‘research-to-practise’* phase, participants in the *Osteo-cise* program will be invited to continue the training program which will be administered by staff at each health and fitness centre with little or no input from the research staff. This translational phase is designed to evaluate the sustainability of the program in the ‘real world’. Participants in both groups will continue to take vitamin D and calcium supplementation over this period dispensed at no personal cost.

### Sample size

In order to calculate the number of participants required for this study, power calculations were performed based on BMD and functional muscle power results from previous exercise intervention trials [37,39]. It was estimated that 60 participants in each group would provide at least 90% power to detect a 1.8% difference (assuming a standard deviation [SD] of 3.5) for the change in femoral neck BMD at p < 0.05 (two-tailed). For functional muscle power, we estimated that 24 participants would provide 90% power to detect a 15% difference for the change between the groups (two-tailed, P < 0.05) assuming a SD of 15%. Therefore with an anticipated 20% dropout rate, a minimum of 72 participants per group will be required (144 in total).

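### The sample-size section claims at least 90% power for femoral neck BMD with 60 per group, but its own inputs give about 80%

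*Protocol article*

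**What the plan says.** The Sample size section gives two calculations.

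- **Femoral neck BMD (a primary outcome).** It states that "60 participants in each group would provide at least 90% power to detect a 1.8% difference (assuming a standard deviation [SD] of 3.5"). The SD of 3.5 applies to the change itself ("assuming a standard deviation [SD] of 3.5) for the change in femoral neck BMD"), and the test is two-tailed at 0.05.
- **Functional muscle power (stair climb, also primary).** It states that "24 participants would provide 90% power to detect a 15% difference for the change between the groups", with an SD of 15%, two-tailed at 0.05. Unlike the BMD sentence, it does not say whether the 24 is per group.

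Allowing for 20% dropout, the section concludes that "a minimum of 72 participants per group will be required (144 in total"). The 72 equals 60 × 1.2, so the BMD calculation sets the trial size. The section mentions no covariate adjustment, repeated-measures correlation or other reduction in variance.

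**The concern.** The BMD sentence supplies everything a two-group power calculation needs: number per group, difference, SD of the change, significance level and sidedness. The result can therefore be checked directly. A standardised difference of about 0.51 with 60 per group is a familiar 80% design, so a claim of at least 90% looks wrong on sight.

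At stake is the sensitivity of the trial on the outcome that fixes its size. If the claim is wrong, the planned type II error is about twice the one stated. A reader of a null BMD result would then credit the trial with more ability to exclude a 1.8% effect than it was designed to have.

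**Working it through.** **Inputs**, all from the Sample size section: n = 60 per group; difference δ = 1.8; SD of change σ = 3.5, on the same percentage scale; two-sided α = 0.05; equal groups.

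**1. Attempt to reproduce the stated power.**

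- Standardised difference: 1.8/3.5 = 0.514.
- Standard error of the difference: σ√(2/n) = 3.5 × √(2/60) = 0.639.
- Normal approximation: power = Φ(1.8/0.639 − 1.960) = Φ(2.817 − 1.960) = Φ(0.857) = 80.4%.
- Exact two-sample t-test (noncentral t): 79.8%.

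The stated figure of at least 90% is not reproduced. The gap is about 10 percentage points.

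**2. Number per group that the inputs imply.**

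n per group = 2σ²(z₀.₉₇₅ + z_power)²/δ²

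| Power | Normal approximation | t-test |
|---|---|---|
| 80% | 2 × 12.25 × (1.960 + 0.842)²/3.24 = 59.4, so 60 | 60.3 |
| 90% | 2 × 12.25 × (1.960 + 1.282)²/3.24 = 79.5, so 80 | 80.4, so 81 |

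The stated n of 60 matches an 80% calculation.

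**3. What would have to change for 90% power at 60 per group.**

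- Difference: about 2.07% (normal) or 2.09% (t-test), in place of 1.8%.
- SD: about 3.04 (normal) or 3.02 (t-test), in place of 3.5.

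**4. Other readings of the paragraph (t-test).**

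| Reading | Power | Fits the text? |
|---|---|---|
| One-sided 0.05, 60 per group | 87.6% | No: two-tailed is stated |
| Two-sided, 72 per group (enrolled) | 86.5% | No: 60 is stated |
| One-sided, 72 per group | 92.3% | No: contradicts both |
| One-sample or paired formula, n = 60 | 97.5% | No: two groups are compared |

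No reading that keeps 60 per group in a two-group comparison reaches 90%. The readings that do reach it contradict the stated design.

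**5. Dropout.** Losing 20% of 72 leaves 72 × 0.8 = 57.6 per group, with power of about 78%. Keeping 60 after a 20% loss would need 60/0.8 = 75 per group.

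**6. Stair-climb figure.** The standardised difference is 15/15 = 1.0. With 24 per group, t-test power is 92.4%, consistent with the stated 90%. With 24 in total (12 per group) it is 64.9%. The figure holds only if 24 means per group.

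**The case against.** **The planned analysis may be more efficient than a t-test.** The Statistical analyses section allows ANCOVA on change and repeated-measures ANOVA. A covariate with a correlation of about 0.5 with the change score would bring 60 per group to about 90% (89.7% by t-test at a correlation of 0.50). This part stands: 79.8% is the power of the calculation as stated, and an adjusted analysis could do better. It does not rescue the sentence. No such correlation is given, the SD is already that of the change, and unadjusted ANOVA remains an option in the same section.

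**The power may not be the wrong number.** The inputs come from earlier trials that cannot be consulted here. The difference, the SD or the n could equally be misstated. This stands too, and it bears on the fix: the first step is to check the source calculation.

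**The practical harm is limited.** 80% is a conventional power level, and results will be presented with 95% confidence intervals, which show the precision achieved whatever power was planned. That limits the risk of misreading a null result, but a wrong figure in the calculation that sizes the trial still needs correcting.

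**The stair-climb wording.** The figures of 60 and 72 are both given per group, so 24 is naturally read the same way and then holds. This is accepted: it is a point of wording, and the main conclusion does not depend on it.

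**Conclusion.** The concern holds. For femoral neck BMD, the stated inputs give 79.8% power (80.4% by the normal approximation), against a claim of at least 90%. The planned type II error is about 20%, where at most 10% is claimed. With a 1.8% difference and an SD of 3.5, 90% power needs 81 analysable participants per group, 21 more than planned.

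This assumes an unadjusted two-group comparison of change, two-sided at 0.05, with all 60 per group analysable. At the anticipated dropout, power is slightly lower, about 78%. A stricter significance level, which the Statistical analyses section allows for multiple comparisons, would lower it further. The document does not show which element of the sentence is misstated; it shows only that they cannot all be right.

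**What to change.** Check the paragraph against the original calculation and correct whichever element is wrong.

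- **If the inputs stand**, restate along these lines: 60 analysable participants per group give 80% power (two-sided 0.05) to detect a 1.8% difference in the change in femoral neck BMD, assuming an SD of 3.5%; the difference detectable with 90% power is 2.1%. This is a rewording with no extra enrolment. The cost is a less favourable stated power.
- **If the difference or SD was mis-transcribed**, give the right value with its source. About 2.09% or about 3.02 respectively would support 90% at 60 per group.
- **If 90% power for 1.8% was the design goal**, 81 analysable participants per group are needed. With 20% dropout that is 81/0.8 = 101.25, so 102 per group and 204 in total, against the planned 144.

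In the same edit, state that the stair-climb figure is 24 per group. Also make the enrolment figure agree with the analysable number: either 75 per group to retain 60, or about 58 analysable (78% power) from 72.

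### The dropout allowance multiplies 60 by 1.2 when it should divide by 0.8, so 72 per group falls short of 60 evaluable at 20% dropout

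*Protocol article*

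**What the plan says.** The Sample size section of the protocol article derives the enrolment figure in three steps.

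- **Evaluable target.** For femoral neck BMD, "60 participants in each group would provide at least 90% power". The effect and spread are given as "detect a 1.8% difference (assuming a standard deviation [SD] of 3.5) for the change in femoral neck BMD", tested two-sided at 0.05.
- **Second primary outcome.** For functional muscle power, 24 participants are said to give 90% power for a 15% difference with an SD of 15%. Whether 24 is per group or in total is not stated. This requirement is the smaller one and does not drive the total.
- **Inflation for dropout.** The enrolment figure then follows as a consequence: "with an anticipated 20% dropout rate, a minimum of 72 participants per group will be required (144 in total".

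The article gives no other inflation rule, no definition of dropout and no replacement rule.

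**The concern.** A dropout rate is a proportion of the people enrolled. To finish with a given number, the target is divided by the proportion retained. Adding 20% of the target to the target is a different operation and always gives a smaller answer. The figure of 72 is exactly what that second operation yields from 60.

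The enrolment number is what recruitment works to, and the section presents it as a floor. If dropout runs at the rate the section itself anticipates, a trial that enrols exactly this floor misses its own evaluable target on a primary outcome. The error is in the unsafe direction, and it adds to a power statement that is already too high for the inputs given.

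**Working it through.** **Inputs, all from the Sample size section:** evaluable target 60 per group; dropout 20%; enrolment 72 per group, 144 in total; difference 1.8%; SD 3.5, taken to be in the same percentage units; two-sided alpha 0.05.

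**1. Reproducing the stated figure.** 60 × (1 + 0.20) = 72. The plan's number comes out exactly, but only by this form.

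**2. The correct form.** Enrolled = evaluable / (1 − dropout) = 60 / 0.80 = 75 per group, 150 in total. Check: 75 × 0.80 = 60.

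**3. What 72 delivers.** 72 × 0.80 = 57.6 per group, about 115 in total against the 120 required. The dropout rate at which 72 still leaves 60 is 1 − 60/72 = 16.7%.

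**4. Effect on power for femoral neck BMD.** The standardised difference is 1.8 / 3.5 = 0.514. By normal approximation, power = Φ(δ / (SD × √(2/n)) − 1.96).

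- At n = 60: 3.5 × √(2/60) = 0.639; 1.8 / 0.639 = 2.817; Φ(0.857) = 80.4%.
- At n = 57.6: 3.5 × √(2/57.6) = 0.652; 1.8 / 0.652 = 2.760; Φ(0.800) = 78.8%.

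| Evaluable per group | Normal approximation | t-test |
|---|---|---|
| 57.6 | 78.8% | 78.1% |
| 60 | 80.4% | 79.8% |

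The inflation step alone costs 79.8 − 78.1 = 1.7 points (1.6 by normal approximation). At 57.6 per group, 90% power (t-test) is reached only for a difference of 2.13%.

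**5. Separating this from the other error.** Even with all 60 evaluable, power is about 80%, against the stated "at least 90% power to detect a 1.8% difference". So about 10 points of the gap come from the power calculation and fewer than 2 from the dropout step. Reaching 90% with the stated inputs takes 2 × (1.960 + 1.282)² × 3.5² / 1.8² = 79.45, so 80 evaluable per group (81 by t-test). With 20% dropout that is 80 / 0.8 = 100 enrolled per group (81 / 0.8 = 101.25, so 102, by t-test).

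**6. Functional muscle power.** With a difference equal to one SD, 22 to 23 per group gives 90% power. At 57.6 evaluable this outcome is not at risk.

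**The case against.** The strongest reply concerns size, not arithmetic.

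- **The loss is slight.** It amounts to 2.4 evaluable per group and under two points of power, and the other primary outcome is unaffected. This stands: the slip alone is unlikely to change what the trial concludes.
- **The figure of 72 is only a floor.** Recruiting more is not barred. True, but a floor should meet the requirement it is derived from, and this one does not.
- **Not every dropout is lost to the analysis.** The Statistical analyses section plans intention-to-treat comparisons after 12 and 18 months, and Table 3 schedules DXA at both. Someone who leaves after month 12 still supplies a 12-month BMD, and the section does not say at which time point the 20% applies. The 57.6 is therefore a planning figure, not a certain loss at both visits. That tempers the point without rescuing 72: someone lost before month 12 has no follow-up DXA, and the section's own allowance treats dropouts as lost.
- **The shortfall from 90% belongs mostly to another error.** This also stands, and the two must be sized separately, as in step 5 above. Correcting the power claim would not remove this error, though: a revised target of 81 inflated in the same way gives 81 × 1.2 = 97.2, still short of 102.

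**Conclusion.** The concern holds. The section's target, dropout rate and enrolment figure cannot all be right: 72 per group with 20% dropout leaves 57.6, and 60 requires 75. The consequence for power is modest, about 1.7 points, and leaves the BMD comparison at 78% for the stated 1.8% difference. This rests on the stated SD of 3.5, a two-sided two-group comparison at 0.05, equal group sizes, and the usual convention that a dropout contributes no outcome. The figure should be corrected because it is the operative number of the section and is wrong on the section's own terms.

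**What to change.** **Preferred, wording only.** Keep 72 per group and describe it correctly, for example: *Enrolling 72 per group (144 in total) allows for about 17% dropout. At the anticipated 20% dropout, 57 to 58 per group will be evaluable, giving 78% power for a 1.8% difference in femoral neck BMD change (SD 3.5, two-sided 0.05).* This also replaces the 90% power statement for BMD, so the section becomes consistent. It costs nothing in recruitment.

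**If 60 evaluable is to be kept.** State 75 per group (150 in total), which is three more per group and six more overall. The power sentence must still be changed, because 60 evaluable gives about 80%. Moving to 75 does not make the 90% claim true.

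In either case, inflate any revised evaluable target by dividing by 0.8.
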